#### Assessment of the primary endpoint

The primary success will be assessed intraoperatively in the CRF. A copy of the intraoperative radiography will be recorded in addition.

#### Secondary endpoints

• Duration of port implantation procedure

• Perioperative complication rate

• Postoperative complication rate

### Safety aspects

#### Specification of safety parameters

#### Training for surgeons

All surgeons will be briefed and trained in both techniques. The correct placement of the port catheter will be checked after operation with x-ray and recorded in the CRF.

#### Concomitant medication

Concomitant medication will not be recorded because an interaction between surgical technique and medication of the patients is unlikely and will therefore not be expected. This decision was met in total agreement of all involved study physicians.

#### Past medical history

Prior and concomitant illness of the patients will be documented in the CRF because discussions between all involved study physicians resulted in the opinion that an interaction between concomitant illness and intervention will be indeed unlikely but could not completely be excluded.

#### Adverse events and serious adverse events

AEs will be reported to the principle investigator in regular intervals throughout the study. Symptoms anticipated by Chemotherapy and malignant illness progress and therefore unlikely related with the surgical implantation technique will not be recorded as AE.

SAEs which are meet one of definitions of the secondary endpoints are treated as SAEs regarding to documentation but have not to be reported to the sponsor/principle investigator within 24 h. They will be reported to the principle investigator in regular intervals throughout the study.

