## Background

### Totally Implantable Access Ports (TIAP)

Insertion of a Totally Implantable Access Port (TIAP) is a routinely employed technique in patients who need a save and permanent venous access for e.g. chemotherapy and/or parenteral nutrition[1]. This system needs no external dressing, allows the patient normal physical activity, is probably less prone to infectious complications and will minimize the occlusion rate of the catheter compared to non-totally implantable catheters[1]. TIAPs are being extensively used world-wide and an increase of port placement can be expected with the broader introduction of innovative therapies in oncology such as the Capri Protocol in pancreatic cancer[2].

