## Study design

### Aim of study

The objective of this trial is to compare the success and complication rates of two different implantation techniques for TIAP: Venae Sectio of the cephalic vein and direct insertion of the port catheter versus Venae Sectio and insertion of the port catheter with a guide wire and peel away sheath (modified Seldinger Technique).

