### Eligibility

#### Inclusion criteria

• Benign and malignant diseases which demand a safe and permanent venous access, e.g. for chemotherapy and/or parenteral nutrition

• Age equal or greater than 18 years

• Patients scheduled for primary elective implantation of a port-catheter-system in local anaesthesia

• Informed consent

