#### Minimizing measurement bias

An independent nurse will document and monitor the procedure in the operating theatre. Blinding is not possible and necessary due to the research question.

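### The AE rule leaves out events expected from chemotherapy or tumour progression, so non-serious events that could also be port complications can go unrecorded

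*Protocol article*

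**What the plan says.** The rule stands in the protocol article under Adverse events and serious adverse events: "Symptoms anticipated by Chemotherapy and malignant illness progress and therefore unlikely related with the surgical implantation technique will not be recorded as AE". The paragraph after it deals with serious events only: "SAEs which are meet one of definitions of the secondary endpoints are treated as SAEs regarding to documentation". For these, only the 24-hour report is waived.

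Complications belong to the trial's purpose. Aim of study reads "The objective of this trial is to compare the success and complication rates of two different implantation techniques for TIAP", and the secondary endpoints include "Postoperative complication rate" alongside a perioperative rate. Study organization also lists the frequency or severity of AEs among the reasons for ending the trial.

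On assessment, Minimizing measurement bias says "Blinding is not possible and necessary due to the research question". The independent observer is described for the operation only: "An independent nurse will document and monitor the procedure in the operating theatre".

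The population includes "Benign and malignant diseases which demand a safe and permanent venous access, e.g. for chemotherapy and/or parenteral nutrition". The background says that the port system, compared with catheters that are not fully implanted, "is probably less prone to infectious complications and will minimize the occlusion rate of the catheter".

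**The concern.** The weak step is the inference inside the rule. An event expected from chemotherapy or from the tumour is not for that reason unlikely to come from the port. Where the two causes produce the same picture, expectedness says little about which one was at work. The rule nevertheless settles causality before anything is written down. A relatedness judgement on a recorded event can be reviewed and reversed, but an event that was never entered cannot.

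Two things are at stake. One is the safety record on which a decision to end the trial may rest. The other is the comparison of postoperative complications between techniques, in so far as it draws on AE entries.

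**Working it through.** The article gives no complication rate, no length of follow-up and no share of events that the rule would remove. Its only sample-size figure concerns the primary endpoint, and this point does not depend on it. The check is therefore mainly a reading of the sections side by side.

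**1. Reach of the rule.** It applies to patients with cancer or on chemotherapy. Chemotherapy is a named indication for the port (Inclusion criteria), so the rule can apply to many participants.

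**2. Overlap with port complications.** The background names infection and occlusion as catheter problems. Infection in a patient on chemotherapy fits both descriptions: an expected effect of treatment and a possible port complication. This one example is enough to break the inference.

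**3. Backstop.** The paragraph on SAEs keeps an event documented if it is serious and meets a secondary-endpoint definition. A non-serious event has no stated exemption. Nor does the paragraph say expressly that it overrides the exclusion.

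**4. Who judges, and whether the judgement can be checked.** There is no blinding, and no independent assessor is described after the operation. Concomitant medication is not recorded (Concomitant medication), so an attribution to chemotherapy may be hard to verify from the CRF.

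**5. Consistency.** Under Past medical history, earlier and concurrent illness is recorded because an interaction, though thought unlikely, could not be ruled out. For AEs, being thought unlikely is enough to leave the event out. The same standard applied to AEs would lead to recording.

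**6. Illustration of size (all rates assumed).** Inputs: n = 80 analysed per arm (CONSORT table), two-sided 5% level (sidedness assumed), true complication rates p1 and p2, and a share m of events lost equally in both arms.

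- Observed rates: q1 = p1(1 − m), q2 = p2(1 − m)
- Observed difference: (p1 − p2)(1 − m)
- Risk ratio: q2/q1 = p2/p1, unchanged
- Power = Φ{[(q1 − q2) − 1.96·√(2q̄(1 − q̄)/n)] / √([q1(1 − q1) + q2(1 − q2)]/n)}, where q̄ is the mean of q1 and q2

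As a check on the formula, the primary-endpoint rates of 80% and 95% give 82.5% power at 80 per arm, against the 80% that the article states.

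For p1 = 15%, p2 = 5%, m = 30%: q1 = 10.5%, q2 = 3.5%, q̄ = 7%. The numerator is 0.070 − 1.96 × 0.0403 = −0.0091 and the denominator is 0.0400. Power = Φ(−0.227) = 41%.

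| Share lost, both arms | Difference (points), 15% vs 5% | Risk ratio | Power, 15% vs 5% | Power, 10% vs 5% | Power, 20% vs 10% |
|---|---|---|---|---|---|
| 0% | 10 | 0.33 | 56% | 22% | 42% |
| 10% | 9 | 0.33 | 51% | 20% | 38% |
| 30% | 7 | 0.33 | 41% | 17% | 30% |
| 50% | 5 | 0.33 | 30% | 13% | 22% |

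The difference and risk-ratio columns refer to 15% vs 5%. Equal loss costs events and absolute difference. It does not distort the risk ratio.

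**The case against.** The strongest reply is that the rule governs what is recorded as an AE, and nothing in the endpoint or analysis sections says that the complication endpoint is built from AE records. The SAE paragraph shows that endpoint definitions exist. A condensed article may leave them to the full protocol, and they may already cover infection. The authors name infection and occlusion as catheter problems, so they may never have meant the rule to remove them. This stands against any claim that the endpoint is in fact under-counted. It does not answer the gap for non-serious events, nor the use of AE frequency as a reason to end the trial, which depends on AE records directly.

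A reader might also infer that the rule favours one technique. The documents do not support that. The rule is the same for both arms, both use the dissected cephalic vein, and no reason appears why later symptoms would be attributed differently. Distortion of the ratio needs unequal loss. For example, with assumed rates of 15% and 5%, loss confined to the lower-rate arm would move the risk ratio from 0.33 to 0.30 (10% lost) or 0.17 (50% lost). Lack of blinding makes this possible, but nothing shows that it would happen.

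A reader might extend the examples to sepsis or thrombosis. The article names neither, and sepsis would normally be serious, so it would stay documented if it met an endpoint definition. Infection carries the argument without them.

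**Conclusion.** The point holds in a limited form. As written, the rule allows non-serious events that could be port complications to go unrecorded, on a presumption of cause that does not follow and on an attribution made without blinding. AE-based safety monitoring can be under-counted. The postoperative complication rate can be under-counted too, on the assumption that it draws on these records.

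The size cannot be derived from the article. The table shows what equal loss would do under assumed rates and is not an estimate for this trial. The primary endpoint is assessed during the operation and is not touched, so the trial's main conclusion is not at risk. The change is worth making because it is cheap and because the lost information cannot be recovered later.

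**What to change.** Amend the paragraph on adverse events in three respects:

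- Record every event that meets a perioperative or postoperative complication definition, or that could plausibly be a port or catheter complication (such as infection or catheter occlusion), whatever its presumed cause.
- Enter relatedness as a separate field, judged after the event is recorded.
- Limit the non-recording rule to symptoms that cannot be port complications.

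Report the complication endpoint by its definition, and add a supportive count regardless of attribution. The endpoint itself should not be replaced by a count of all recorded events, since that would bring chemotherapy-related infections into the comparison as background noise.

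The cost is a few more entries in the existing eCRF, some of which will turn out to be chemotherapy-related. Sample size and the primary analysis do not change.

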### Analysis

Comparisons will be made of the primary endpoints of both intervention groups for all in the study included patients on an intention to treat basis. Furthermore there will be a second analysis on a "per protocol" basis including only patients who get strictly treated according to the study protocol. The outcome measures of the primary endpoint will be tested for significance with the chi square test.

### Study organization

All patients scheduled for a primary port-catheter-system implantation procedure in the Outpatient-Clinic of the Department of Surgery, University Hospital of Heidelberg, will be referred to the Centre for Clinical Studies in Surgery (KSC) and screened by members of the KSC [4]. The result of the screening will be recorded in the screening-log.

Approximately 500 patients per year undergo a port-catheter-system implantation at the Outpatient-Clinic of the Department of Surgery, University of Heidelberg. The estimated time frame to randomize 180 patients is approximately 18 months.

The independent data management and monitoring will be done by the Coordination Centre for Clinical Trials (KKS) Heidelberg.

The principal investigator has the right to terminate the trial and to remove all trial material from the trial centre at any time in consultation with the Clinical Study Team Leader and the Biometrician. Reasons that may require a termination of the trial include the following:

• The incidence or severity of adverse events in this trial indicates a potential health hazard caused by the study treatment

• It appears that patient's enrolment is unsatisfactory with respect to quality and/or quantity or data recording is severely inaccurate and/or incomplete

• External evidence that makes it necessary to terminate the trial

### Financial support

One half of the costs for this study will be financed by the Surgical Foundation Heidelberg (Stiftung Chirurgie Heidelberg), the other half will be sponsored by Fresenius Kabi AG ^©^. This concept of a half-half financial support will help to guarantee the independency of the final study analysis and its results from commercial interests.

**Table 1 T1:** Flowchart according to CONSORT

	To be assessed for eligibility (n = 280)	
		Total to be excluded (n = 100) refusal to participate (n = 40) not meeting inclusion criteria prior to surgery (n = 20) no cephalic vein present (n = 20) other reasons (n = 20)
	To be randomized (n = 180)	
Experimental Group		Control Group
To be allocated to intervention (n = 90) receive allocated intervention (n = 80) don't receive allocated intervention (n = 10)		To be allocated to intervention (n = 90) receive allocated intervention (n = 80) do not receive allocated intervention (n = 10)
To be analyzed (n = 80)		To be analyzed (n = 80)

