**Study design:**

A single-centre, randomized, controlled superiority trial to compare two different TIAP implantation techniques. Sample size: 160 patients will be included and randomized intra-operatively. Eligibility criteria: Age equal or older than 18 years, patients scheduled for primary elective implantation of a TIAP in local anaesthesia and a signed informed consent. Primary endpoint: Primary success rate of the randomized technique. Intervention: Venae Sectio in combination with the Seldinger Technique (guide wire and a peel away sheath) will be used to place a TIAP. Reference treatment: Conventional Venae Sectio will be used with a direct insertion of the TIAP without guide wire or peel away sheath. Duration of study: Approximately 20 months.

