#### Patients needed

If the real success rate difference is minimum 15% (80% vs. 95%) then there is a 80% chance that a trial involving 160 patients could detect a significant difference at a level of 5%.

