### Randomization and procedures for minimizing bias

#### Minimizing systematic bias

In order to achieve comparable groups for known and unknown risk factors a block randomization will be performed by the randomization software RITA^®^. A sufficient number of patients will be recruited according to the sample seize calculation in order to prevent random error. Patients will get randomized intra operatively after identification of the cephalic vein in order to minimize post randomization drop outs.

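### Table 1 analyses only the 80 per arm who receive the allocated technique, while the Analysis section promises intention to treat for everyone included; the two primary analysis sets must be reconciled

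*Protocol article*

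**What the plan says.** The Analysis section sets the primary comparison "for all in the study included patients on an intention to treat basis". It then adds a second analysis on a per-protocol basis and names the chi-square test for the primary endpoint.

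Table 1 (the projected CONSORT flow chart) randomises 180 patients, 90 per arm. In each arm 80 receive the allocated technique and 10 do not; the experimental column reads "don't receive allocated intervention (n = 10"). The last row of each column is "To be analyzed (n = 80"). No row shows 90 analysed, and nothing labels the 80 as a per-protocol set.

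Under Patients needed the article says "there is a 80% chance that a trial involving 160 patients" would find a difference of 80% against 95%. The abstract says "160 patients will be included and randomized intra-operatively", whereas Study organization and Table 1 both give 180 as the number to randomise.

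The primary endpoint is success of the randomised technique, judged during the operation by catheter position and function. Randomisation comes late: "Patients will get randomized intra operatively after identification of the cephalic vein in order to minimize post randomization drop outs". Patients without a usable vein leave before that point and have their own exclusion line in Table 1.

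**The concern.** An intention-to-treat comparison keeps every randomised patient in the allocated arm. Table 1 leaves out 20 of 180 (11.1%), chosen by something that happens after randomisation in an unblinded operation. A reader who follows the table runs a different primary analysis from a reader who follows the text, and nothing in the article says which governs.

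The choice matters more here than in most trials because receipt of the technique and the endpoint lie close together. The Medical problem section names an undersized vein or an obstacle on the way to the vena cava as a major cause of failure. Either can show itself after the vein has been exposed and the patient randomised. A patient in whom the allocated technique is given up for such a reason has failed on the primary endpoint, yet could be recorded as not having received the allocation and drop out of the denominator. If the choice between 90 and 80 per arm stays open, it can be made once results are known.

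**Working it through.** **Inputs.** Success 80% against 95%, 5% level, 80% power, 160 patients (Patients needed); 90 randomised, 10 not treated as allocated and 80 analysed per arm (Table 1); chi-square test (Analysis). The article does not state sidedness; two-sided is assumed.

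**1. The plan's own figure.** Power at 80 per arm for 80% against 95%:
- Fisher's exact test: 79.3%, which reproduces the stated 80%.
- Chi-square, pooled normal approximation: 82.5%.
- Chi-square, exact binomial enumeration: 84.9%.

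The figure of 160 is therefore not itself at fault.

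**2. Which set the 160 belongs to.** 90 − 10 = 80 per arm, and 80 + 80 = 160. Conversely, 160 / (1 − 20/180) = 180. The 180 equals the powered 160 inflated for the 20 patients who are then left out, so the sample size matches the set in Table 1, not all randomised patients.

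**3. Effect of exclusion on an estimated rate.** Take 72 successes in 90 = 80.0%. If all 10 excluded are failures, the rate becomes 72/80 = 90.0%, a shift of 10 points against a target difference of 15. If 5 are failures and 5 successes, it is (72 − 5)/80 = 83.8%.

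**4. Effect on the false-positive rate.** Assume no true difference, with 85% success in both arms, 90 randomised and 10 removed per arm, and a chi-square test at two-sided 5%. Removing 5 failures and 5 successes moves an arm's expected rate from 76.5/90 = 85.0% to (76.5 − 5)/80 = 89.4%. By simulation:

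| Removal | Rejection rate |
|---|---|
| Random in both arms | 4.8% |
| 5 failures and 5 successes from each arm | 11.6% |
| 5 failures and 5 successes from one arm, random in the other | 16.5% |

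**5. Intention-to-treat power at 90 per arm** (exact chi-square). The 80 receivers contribute 0.80 × 80 = 64 and 0.95 × 80 = 76 expected successes.

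| Assumption for the 10 non-receivers per arm | Rates | Power |
|---|---|---|
| All 180 follow the planned rates | 80% vs 95% | 89.0% |
| They take the other arm's rate | (64 + 9.5)/90 = 81.7% vs (76 + 8)/90 = 93.3% | 67.7% |
| All are failures | 64/90 = 71.1% vs 76/90 = 84.4% | 57.8% |

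**6. Are all 10 failures plausible?** At 95% success the experimental arm expects 0.05 × 90 = 4.5 failures, and the probability of 10 or more is about 1.5%. The control arm at 80% expects 0.20 × 90 = 18, so 10 failures fit there easily.

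**The case against.** The strongest defence is that the Analysis section is the only place that names the primary analysis, and it names intention to treat. Table 1 is a projection, and its 80 + 80 fits the announced per-protocol analysis. This defence stands in part. A reader might infer from the table that the planned primary analysis is not intention to treat; the article does not support that, because the text says the opposite. What remains is a conflict: the table has a single analysed row, without a label, and it coincides with the 160 on which the power rests.

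A reader might also infer that the 10 per arm are mostly technique failures. No section gives their reasons, and the Subject withdrawal criteria also allow for the patient's own request and for the patient's well-being. In the experimental arm, 10 failures among non-receivers would sit badly with the assumed 95% (step 6). Removal of failures is possible, and its direction depends on the reasons in each arm.

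Thirdly, a reader might conclude that intention to treat cannot reach the stated 80% power. That holds only if the planned rates apply to receivers alone and non-receivers fare differently. If all 180 follow 80% against 95%, power is about 89%. The 80% comes from the department's series of the conventional approach. If that series already counted abandoned attempts as failures, adding non-receivers as further failures would count them twice.

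**Conclusion.** The contradiction is certain: the text analyses everyone included, the table analyses only those treated as allocated, and the sample size follows the table. It concerns the primary analysis set and should be settled before any outcome is seen.

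Its consequences are conditional. Following Table 1 could shift one arm's rate by up to 10 points and raise the false-positive rate to about 12–17% in the scenarios shown, but it leaves that rate at about 5% if removal is unrelated to outcome. It would therefore be too strong to say that the type I error is broken. Likewise, intention-to-treat power with 180 randomised lies between about 58% and 89%, depending on an assumption the article does not make. All figures assume a two-sided 5% test and Table 1's 10 non-receivers per arm.

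**What to change.** - In Table 1, show 90 and 90 analysed for the primary intention-to-treat comparison, and label 80 and 80 as the per-protocol set.
- In the Analysis section, state that every randomised patient is analysed in the allocated arm, and that a patient in whom the allocated technique is abandoned or not achieved counts as a primary failure there. This follows the endpoint definition already given. State also how non-receipt for other reasons, such as the patient's request, is counted.
- Under Patients needed, give the intention-to-treat power for 180 randomised as a range with its assumptions: about 89% if all follow 80% against 95%, about 68% if non-receivers take the other arm's rate, and about 58% if all non-receivers are failures on top of the planned rates.
- Reconcile the 160 randomised in the abstract with the 180 in Study organization and Table 1.

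The cost is some wording, one table row and possibly a less favourable stated power. No patients are needed beyond the planned 180.
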